## Participant timeline {13}

This study will be carried out between December 2020 and November 2022. Figure 2 shows the schedule of enrollment, interventions, and assessments (according to the SPIRIT).

**Fig. 2 Fig2:**
[figure not shown]
Schedule of enrolment, interventions, and assessments (according to SPIRIT)

### Sample size {14}

Sample size calculations were performed with G*Power 3.1.9.4 (Düsseldorf, Germany) based on the therapy effects on pain and accounting for a 10% loss to follow-up after 4 months. Calculations were based on one-tailed testing with alpha set in 0.025, partial η2 = 0.04, and the desired power of 0.95. The allocation ratio (N2/N1) was defined as 1, resulting in 35 patients in the intervention group and 35 in the control group.

### Recruitment {15}

We will recruit participants through practitioners from Iran University of Medical Science’s hospitals and clinics. Also, we will use advertising posters in each center and online advertisements on the media. Then, the participants will be referred to the outpatient orthopedic rehabilitation center at the School of Rehabilitation Sciences. They will be screened for inclusion and exclusion criteria and make the final decision regarding the eligibility of the patients.

## Assignment of interventions: allocation

### Sequence generation {16a}

After eligibility has been confirmed, patients will be informed about the study comparing two physiotherapeutic treatment options. After obtaining written informed consent, baseline measurements will be performed. Participants then will be randomized to either active control or experimental group (1:1 ratio) using a stratified block allocation with stratification factors being gender (male or female) and with a block size of four. Randomization will be done at the Iran University Medical Sciences by an independent investigator using WinPepi (version 11.65). The randomization schedule will be known only to 1 investigator who is not involved in recruiting participants.

### Concealment mechanism {16b}

The randomization will be concealed from patients, and the other investigators involved in patient assessments, treatments, and analyses.

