## Interventions

### Explanation for the choice of comparators {6b}

After obtaining written informed consent, baseline measurements will be performed. Participants will then be randomized to either active control or experimental group (1:1 ratio) using a stratified block allocation with stratification factors being gender (male or female) and with a block size of four. Randomization will be done at the Iran University Medical Sciences by an independent investigator using WinPepi (version 11.65). The randomization schedule will be known only to 1 investigator who is not involved in recruiting participants. The randomization will be concealed from patients and the other investigators involved in patient assessments, treatments, and analyses.

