### Intervention description {11a}

All interventions are performed by two expert and trained physiotherapists with 6 years of work experience in the treatment of LBP patients. The intervention lasts six weeks and each group will receive 12 sessions of physiotherapy.

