### Primary outcome

The pain will be assessed through a self-reported questionnaire. This questionnaire will be used for pain assessment at baseline, post-treatment, and at 1 and 4 months follow-up:
A Numerical Rating Scale (NRS) for pain ranging from 0 “no pain at all” to 10 “worst imaginable pain” (“How would you rate your low back pain, on average, over the last 3 days?”) [37].

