## Assignment of interventions: blinding

### Who will be blinded {17a}

The present study is a triple-blind randomized controlled trial. The patients, investigator, and outcomes assessor will be blind to the treatment groups. To keep patients unaware of any expected treatment group benefit, patients will be informed that the effect of 2 well-established therapies is to be evaluated. An independent and blinded assessor will perform the baseline and follow-up assessments. The researcher who will perform the statistical analyses will not be involved in taking the measurements. The treating physiotherapists will be blinded to the results of the measurements and questionnaires.

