## Discussion

This study aims to compare usual care physiotherapy and multidimensional physiotherapy in CNSLBP patients. The main study question is multidimensional physiotherapy is effective in reducing pain associated with CNSLBP. Further objectives are as follows: to evaluate the effect on brain function, disability, quality of life, lumbar forward flexion ROM, and psychosocial factors related to pain with the inclusion of 70 patients with CNSLBP. The patients, assessors performing the baseline and follow-up evaluations, and the researcher performing statistical analyses are blinded to group allocation. Hence, the study is designed in a way that minimizes potential biases. It is expected that this randomized controlled trial will provide novel data on the effectiveness of a multidimensional when compared to usual care physiotherapy on key patient-centered outcome measures.

In the past studies, most therapeutic approaches to the treatment of chronic low back pain were consistent with biomedical models. In these models, the focus is on structural and biomechanical disorders. Recent studies have shown that pain has sensory, behavioral, and cognitive components, and the association of chronic low back pain with cognitive, behavioral, and social factors has been established. As a result, new biopsychosocial models for the treatment of chronic pain have been introduced, but the implementation of these approaches is not yet common, and the number of studies that have examined the multidimensional treatment of low back pain has been limited. Research has shown that people with chronic low back pain undergo cognitive and emotional changes, but it is unclear what functional changes occur in the central nervous system, especially the brain, and our information is limited.

This study aims to investigate the effect of a multidimensional treatment in comparison with usual physiotherapy on clinical and functional outcomes in patients with nonspecific chronic low back pain. Also, in this study, we evaluated the effects of treatment on the central nervous system and changes in thalamic cortical dysrhythmia pattern in the cerebral band spectra (quantitative evaluation), and we are hopeful that this 4-month prospective trial may contribute towards refining guidelines for good clinical practice and may be used as a basis for health authorities’ recommendations.

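### The trial is labelled triple-blind with patients blind to group, but patients are masked only to the expected benefit, so the claim of minimised bias does not hold for self-rated pain

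*Protocol article*

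**What the plan says.** The Abstract and Trial design {8} label the study triple-blind, and Who will be blinded {17a} repeats it: "The present study is a triple-blind randomized controlled trial". That section continues: "The patients, investigator, and outcomes assessor will be blind to the treatment groups". The measure it describes for patients is to tell them that two established treatments are being evaluated, so that they do not know which arm is expected to do better. Of the therapists it says: "The treating physiotherapists will be blinded to the results of the measurements and questionnaires". Of the person doing the statistical analysis it says only that this person takes no measurements.

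Concealment mechanism {16b} consists of one sentence: "The randomization will be concealed from patients, and the other investigators involved in patient assessments, treatments, and analyses". Almost the same sentence closes section {6b}, directly after the statement that a single investigator knows the schedule.

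On delivery, Intervention description {11a} says: "All interventions are performed by two expert and trained physiotherapists with 6 years of work experience in the treatment of LBP patients". On the primary outcome: "The pain will be assessed through a self-reported questionnaire". This is a 0 to 10 rating of average low back pain over the last 3 days.

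The Discussion lists patients, assessors and the analyst as blinded to allocation, and concludes: "Hence, the study is designed in a way that minimizes potential biases".

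**The concern.** Blinding a patient to group means that the patient does not know which treatment is being given. Here the treatments are recognisably different. A patient who attends sessions on anxiety, interpersonal conflict, stigma and sleep, and practises feared movements step by step, knows that this is what he or she is receiving. Hiding the hypothesis is worthwhile, but it is a different and weaker protection.

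The distinction matters because the patient supplies the primary measurement. When the patient knows the treatment and also rates the outcome, a difference in pain scores can partly reflect expectation. A blinded assessor who hands over the form does not remove that. The Discussion nevertheless derives minimised bias from the blinding without separating self-rated from measured outcomes, and it hopes that the results will inform guidelines and health-authority recommendations. A reader who relies on the label would give the pain result more certainty than the design supports.

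**Working it through.** The plan gives no figure on this point, so the check sets the sections side by side.

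**1. Can patients be blind to group?**
- Experimental group: twelve 30-minute psychoeducation sessions, graded exposure, lifestyle advice, postural correction and electrotherapy.
- Active control group: education on spinal anatomy, ergonomics and posture, general trunk exercise and electrotherapy.
- Sequence generation {16a}: patients are told before randomisation that two treatment options are compared. The consent form covers the treatment plans.
- Section 17a: the one patient measure conceals the expected benefit.

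Nothing described conceals the treatment received. The statement that patients are blind to group is stronger than the procedure given to support it.

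**2. Which three parties make the trial triple-blind?**

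| Party | 17a | Discussion |
|---|---|---|
| Patients | blind to group | blinded to allocation |
| Assessor | blind to group | blinded to allocation |
| Investigator | blind to group, role not defined | not listed |
| Analyst | takes no measurements | blinded to allocation |
| Treating physiotherapists | blinded to measurement results only | not listed |

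The two lists agree only if the investigator in 17a is the analyst. The section on informed consent {26a}, however, uses the same word for the person who performs the assessments. For the analyst, 17a describes separation from measurement, which is not blinding.

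**3. Which outcomes does assessor blinding protect?**
- Patient-rated: pain NRS (primary), PCS, TSK, FABQ, SF-36 and ODI.
- Measured: finger-to-floor distance and EEG power.

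Assessor blinding acts mainly on the second group. The primary outcome is in the first.

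**4. Does the Discussion's inference follow?** Its premise is that patients, assessors and analyst are blinded to allocation. By step 1 the premise fails for patients, and by step 3 the patient is the rater of the primary outcome. The inference can stand for the measured outcomes, but not for pain.

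**5. Illustration under assumed values.** The documents do not give the size of any reporting bias. Suppose there is no true effect, 35 patients per arm, a simple comparison of two means at two-sided 0.05, and a reporting difference of b standard deviations in favour of the experimental arm. The chance of a significant result in that direction is

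P = Φ(b / √(2/35) − 1.96), with √(2/35) = 0.239.

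| Assumed b (SD) | b / 0.239 | P |
|---|---|---|
| 0 | 0 | 2.5% |
| 0.1 | 0.418 | 6% |
| 0.2 | 0.837 | 13% |
| 0.3 | 1.255 | 24% |
| 0.5 | 2.092 | 55% |

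With the planned 10% loss (31.5 per arm), the values for b from 0.1 to 0.5 are 6%, 12%, 22% and 51%. This shows only that a modest bias would matter in a trial of this size. It is no evidence that such a bias exists.

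**The case against.** The strongest reply concerns the therapists. A reader might infer from section 16b that the protocol claims to hide the arm from the people who deliver it, which would be impossible. The documents do not support that reading firmly. The sentence stands under the concealment heading, and its twin in {6b} directly follows the sentence about who knows the schedule, so it can mean that the sequence is hidden before assignment. That is feasible, and with a block size of four it is a useful safeguard. Section 17a does not count therapists among those blind to group and limits their blinding to measurement results. This reply stands: the fault in 16b is an unstated time limit, and removing treating staff from the sentence would remove a legitimate protection.

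A reader might also infer that patients have no protection, or that the experimental arm gets more attention. Neither is established. Both arms have twelve sessions twice a week, the same TENS, heat and ultrasound, education, postural-correction training and daily home practice. The 30 minutes is given for psychoeducation alone, and total session length is given for neither arm.

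Finally, the absence of expectancy ratings or arm-guess questions could be read as an error. Such items are optional, a condensed article need not list them, and recruitment began on December 1, 2020, so a rating after the first session could not be obtained from patients already past it.

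It can also be said that the two lists of blinded parties agree if the investigator means the analyst, and that minimising bias is not eliminating it. The first is possible but has to be guessed. The second does not rescue the inference for pain, because its premise of patient blinding is not met.

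**Conclusion.** The point holds as a matter of labelling and of the conclusion drawn from the label. Patients are masked to the hypothesis, not to the treatment group, and the primary outcome is their own rating. The triple-blind label and the unqualified statement on bias therefore claim more protection for pain than the design gives. The protection is reduced, not absent.

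The size of any resulting bias cannot be derived from the documents; the percentages above rest entirely on assumed values. Sample size, randomisation and analysis model are unaffected. Unblinded therapists and patients are normal in trials of this kind, and having them is not the fault. The conclusion assumes that no further patient masking exists beyond what the article describes. Since the article states its patient measure explicitly and the treatments are visibly different, that assumption seems safe.

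**What to change.** - In the Abstract, Trial design {8} and 17a, replace the triple-blind label with: assessor- and analyst-blinded; patients masked to the study hypothesis only; treating physiotherapists not blinded to allocation. First confirm that the analyst is blinded to group, since 17a states only separation from measurement.
- In 17a, say who the investigator is, and list the same blinded parties there and in the Discussion.
- In 16b and {6b}, keep the reference to those involved in treatments, but state that it is the randomisation sequence that is concealed, and that this lasts until assignment.
- In the Discussion, limit the bias statement to the measured outcomes, and say that pain and the questionnaire outcomes are rated by patients who know their treatment. The active comparator, equal session numbers and shared electrotherapy can be cited as partial protection.

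The cost is rewording and a less favourable design label. No new data collection is needed.

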### Implementation {16c}

Allocation sequence, participant enrollment, and participant assignment to interventions will be performed by an independent investigator who is not involved in assessments, interventions, and any other part of research.

## Assignment of interventions: blinding

### Who will be blinded {17a}

The present study is a triple-blind randomized controlled trial. The patients, investigator, and outcomes assessor will be blind to the treatment groups. To keep patients unaware of any expected treatment group benefit, patients will be informed that the effect of 2 well-established therapies is to be evaluated. An independent and blinded assessor will perform the baseline and follow-up assessments. The researcher who will perform the statistical analyses will not be involved in taking the measurements. The treating physiotherapists will be blinded to the results of the measurements and questionnaires.

### Procedure for unblinding if needed {17b}

Not applicable

## Data collection and management

### Plans for assessment and collection of outcomes {18a}

Not applicable

### Plans to promote participant retention and complete follow-up {18b}

Not applicable

### Data management {19}

Not applicable

### Confidentiality {27}

Not applicable

## Plans for collection, laboratory evaluation, and storage of biological specimens for genetic or molecular analysis in this trial/future use {33}

Not applicable

## Statistical methods

### Statistical methods for primary and secondary outcomes {20a}

Data analysis will be performed using SPSS (version 22) and STATA (version 14.2). Baseline characteristics will be summarized with standard descriptive statistics. Categorical variables will be described with percent and counts. Continuous variables will be described with means and standard deviations. Statistical analysis of the primary and secondary outcomes will be based on the intention-to-treat principle including all randomized patients using an analysis of variance/covariance (ANOVA/ANCOVA). A model including baseline as continuous covariate and group as fixed factors will be used with using Bonferroni post hoc analyses and adjusting for differences in patients’ characteristics at baseline where appropriate will be done. Subgroup analysis of pain catastrophizing variable will be done. For all statistical tests, the significance level will be set at 0.05. Mean difference and standardize Mean difference and their 95% confidence intervals (Cohen’s *D*) will be calculated as are effect sizes.

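### The stated model leaves out gender, the randomisation stratum, and ties any further covariates to baseline differences seen in the data

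*Protocol article*

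**What the plan says.** Randomisation is by "stratified block allocation with stratification factors being gender (male or female) and with a block size of four" (Sequence generation {16a}; the same scheme is given under Explanation for the choice of comparators {6b}).

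The analysis section (Statistical methods for primary and secondary outcomes {20a}) specifies: "A model including baseline as continuous covariate and group as fixed factors will be used". The same sentence continues with Bonferroni post hoc analyses and a clause on adjusting for differences in patients' "characteristics at baseline where appropriate will be done". This applies to every outcome: "Statistical analysis of the primary and secondary outcomes will be based on the intention-to-treat principle". Gender is not mentioned in the statistical methods. No other covariate is named, no criterion for a difference is given, and the adjustment is not labelled a sensitivity analysis.

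**The concern.** Two features of the stated analysis work against each other.

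First, stratifying by gender removes most of the gender variation from the treatment comparison. A model without gender still counts that variation as residual error. If gender is prognostic, the reported standard error is larger than the real sampling variability, so the confidence interval is too wide and some power is lost.

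Second, the only route by which another covariate can enter is an observed baseline difference, judged case by case. In a randomised trial such differences are chance. A covariate is worth adjusting for because it predicts the outcome, not because it happens to be unbalanced. The clause would rarely admit gender, the one factor the design calls for, yet it can admit any other characteristic. The primary model is then not fixed before the data are seen.

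**Working it through.** **The plan's own figure.** The article gives no standard error or error rate for this model; its only related figure is the sample size of 70 (35 per group). That is nearly reproduced as a repeated-measures within-between interaction with four assessments, partial η² = 0.04, alpha 0.025, power 0.95 and a correlation of 0.5. The correlation is an assumption, since the article gives none. The result is N = 62, and 62/0.90 = 68.9, or 69. The point here does not depend on it, so N = 70 is taken as given.

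**Inputs from the article.** N = 70, 1:1 allocation, gender strata, blocks of four, and ANCOVA on baseline and group. The test level is 5% two-sided, one reading of "For all statistical tests, the significance level will be set at 0.05" that also fits "one-tailed testing with alpha set in 0.025" in the sample size section.

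**Assumed inputs.** Half the participants are women; the gender effect is 0, 0.3, 0.5 or 0.8 SD; and there are six further candidate covariates. The article gives none of these. There were 6,000 simulated null trials per setting, with Monte Carlo error of about 0.3 points on type I error and 1% on standard-error ratios.

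**Step 1: omitting gender.** The ratio is the mean model standard error divided by the true SD of the estimate.

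| Gender effect (SD) | Model SE | True SD | Ratio | Type I error without gender | With gender |
|---|---|---|---|---|---|
| 0 | 0.2080 | 0.2079 | 1.00 | 4.5% | 4.7% |
| 0.3 (two runs) | 0.2114; 0.2110 | 0.2100; 0.2092 | 1.01 | 4.6%; 4.1% | 5.0%; 4.6% |
| 0.5 | 0.2170 | 0.2095 | 1.04 | 4.2% | 5.2% |
| 0.8 | 0.2287 | 0.2106 | 1.09 | 3.2% | 5.0% |

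*Check of the standard errors by formula.* With half women and a gender effect of δ residual SDs, omitting gender multiplies the residual SD by √(1 + δ²/4). The simulated residual SD after baseline adjustment is about 0.208 × √70 / 2 = 0.87. Effects of 0.5 and 0.8 are therefore 0.57 and 0.92 residual SDs, and the formula gives 1.04 and 1.10. The simulated model standard errors without versus with gender are 0.2170/0.2085 = 1.04 and 0.2287/0.2073 = 1.10. The slightly lower 1.09 in the table is consistent with Monte Carlo error and with incomplete last blocks leaving a little gender imbalance.

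*Check of the error rates.* 2[1 − Φ(1.96 × 1.036)] = 4.2% and 2[1 − Φ(1.96 × 1.086)] = 3.3%, against 4.2% and 3.2% simulated.

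Half women is the least favourable assumption, because p(1 − p) is largest at p = 0.5.

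**Step 2: covariates chosen after seeing the data.**

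- *Mechanical rule*, adjusting only for candidates whose imbalance has p < 0.10: type I error was 3.5-4.7% for gender effects up to 0.5 SD. At 0.8 SD it was 3.2%, the same as with no selection, so that shortfall comes from omitting gender.
- *Most favourable of eight models*, with a gender effect of 0.3 SD: 6.5-6.9% when the covariates have no effect, 9.9% when each has an effect of 0.2 SD, and 12.5% at 0.3 SD each. With non-prognostic covariates and a gender effect of 0.8 SD it was 5.2%, because the two errors roughly cancel.

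**Step 3: after the change.** With gender in the model, type I error is 4.6-5.2% and the standard-error ratio is 0.98-1.00. The residual degrees of freedom go from 70 − 3 = 67 to 70 − 4 = 66.

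**The case against.** The stated model is described as one that includes baseline and group, which is not an exclusive list. Whether the stratum enters is a detail an article may leave to an analysis plan that is not shown. That stands as far as mere silence goes. However, the article does more than stay silent: it states its own rule for further covariates, and that rule would rarely select a factor balanced by design.

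A reader might infer more than the text supports in three ways.

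- *That the standard errors are simply wrong.* The error exists only if gender predicts the outcome after baseline adjustment, which nothing in the article shows. It is conservative and small for modest effects, and it cannot by itself create a false positive.
- *That the balance gained by stratifying is lost.* It is not. Balance belongs to the allocation and still lowers the real variance of the estimate; only the model-based standard error fails to credit it.
- *That the false-positive rate is about 10%.* That needs someone to pick the model with the most favourable result. The article speaks of adjusting for baseline differences, and a rule close to that wording showed no inflation. Nor does it plan significance tests of baseline characteristics; they are to be summarised descriptively.

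There is also a partial safeguard. Allocation is concealed from those doing the analyses, and the Discussion says the analyst is blinded. This hinders choosing covariates to favour the experimental arm, but it does not fix them in advance.

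**Conclusion.** The point holds as a free improvement, in two parts of unequal weight. The adjustment clause is the more important. It is a stated rule that makes the primary model depend on observed imbalance and sets no criterion. Type I error stays at or below nominal under a mechanical rule (about 3.5-4.7%) and reaches about 6.5-12.5% only in the worst case of choosing the most favourable of eight models from six assumed covariates. The wording does not exclude that case, but does not call for it either.

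The omission of gender is a matter of efficiency. The model standard error is too large by about 1%, 4% or 9% for assumed gender effects of 0.3, 0.5 or 0.8 SD, with type I error as low as about 3.2%; it is correct if gender has no effect. All of these sizes rest on assumed gender and covariate effects, because the article gives none.

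**What to change.** In Statistical methods for primary and secondary outcomes {20a}, specify for every primary and secondary outcome an ANCOVA with group, the baseline value of that outcome and gender, fixed in advance and kept whatever imbalance is observed. Delete the clause on adjusting for baseline differences, or move it to a sensitivity analysis labelled as such. If any other covariate is wanted in the main model, name it before the data are seen.

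The cost is a sentence of text and one degree of freedom. Gender is already recorded for every participant because randomisation needs it, and the sample size stays at 70.
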